### Procedures

A patient is considered to be included in the protocol if he/she meets all of the inclusion criteria and none of the exclusion criteria. Then the patient will be verbally informed of the study and given the opportunity to decide whether he/she wants to participate in the trial on an informed basis without any pressure. Then a written informed consent will be obtained from each participant. Once included, the VISA-A Score, MRI UTE T2* value, FAOS Score, VAS Score, and Tenger Score will be assessed. Within 1 week after being enrolled, the percutaneous radiofrequency coblation will be performed by an experienced surgeon. After the surgery, each patient will randomly take an unmarked, opaque, sealed envelope containing a piece of paper with a unique number from 1 to 38. Then the numbers will be divided into two sets via computing software (https://www.randomizer.org/). All patients respectively entered the intervention group and the placebo group according to their own numbers. Patients of the intervention group will receive ESWT at 6 months post-operatively. At the same time, the patients of the placebo group will also experience sham ESWT’s procedure. Either the radial ESWT or sham ESWT will be administered 4 times at weekly intervals. In all, the treatment protocols for the two groups are similar except for the intervention: radial ESWT. All the outcome measurements will be assessed again at 6 months, 1 year, and 2 years after the surgical procedure.

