**Methods:**

The study is a randomized, controlled trial with patients allocated in a 1:1 ratio to one of two parallel groups. Patients with insertional Achilles tendinopathy who are not satisfied with the effect of conservative treatment will be screened. A minimum of 38 patients will be enrolled after deciding to participate in the trial on an informed basis. Then the intervention group and the control group perform radial ESWT and sham-ESWT respectively at 6 months after percutaneous radiofrequency coblation. The primary outcome will be the Victorian Institute of Sports Assessment Achilles (VISA-A) Score. Secondary outcome measures will be Foot and Ankle Outcome Score (FAOS) scale, visual analog scale (VAS), Tegner Score, and MRI ultra-short echo time (UTE) T2* value. The assessments will occur in 6 months, 1 year, and 2 years, post-operatively. The differences between the 2 groups will be conducted as intention-to-treat basis.

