### Aim, design, and setting

We aim to investigate if radiofrequency coblation associated with ESWT can provide more encouraging outcomes regarding the treatment of the IAT with trustworthy evidence.

This study is a randomized, double-blinded, parallel-group clinical trial (Fig. 1). The 1:1 allocation to either receive radial ESWT or sham-ESWT, after surgery is conducted using computer-generated random allocation sequences and sealed envelopes. The patients of the placebo group will also experience ESWT’s procedure, while the apparatus’ therapeutic head will be placed a support, which will block the propagation of shock waves without changing the equipment’s appearance, noise, and using process. Furthermore, the patients will feel the vibration of the machine, but the insertional region won’t be directly stimulated. The physiotherapists will not take any part in the posttreatment assessment of the patients. The outcome data will be collected by research fellows who are blinded to the treatment procedures to reduce the risk of assessment bias. The SPIRIT Figure shows in detail the schedule of enrollment and assessments (Fig. 2).

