### Sample size

The primary outcome of this study is the VISA-A score. McCormack J et al. [32] have identified the minimum clinically important difference (MCID) of 6.5 points for the VISA-A. The study of Wei M et al. [33] indicates an expected standard deviation (SD) of 6.9 points. We have referred to the sample size calculation method of Kvalvaag E et al. [34]. To detect a difference in results between the radical ESWT and the sham-ESWT participants at a level of 5% significance and the most likely scenario for 80% power, 15 patients per group will be needed. Assuming a margin of 20% loss of primary outcome data, we propose to recruit a minimum of 38 patients in total.

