## Trial status

Protocol Amendment Number: 02. Issue Date: 1 Aug 2020. The randomized trial is currently enrolling participants. Recruitment began in October 2018 and the approximate date when recruitment will be completed in October 2021. The end of the trial will be defined as the collection of 2 years of outcome data from the last participant.

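### Allocation is placed after surgery although the arms differ only from month 6, so losses in between become post-randomisation losses

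*Protocol article*

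**What the plan says.** Procedures gives the order of events: consent, baseline measurements, coblation within a week of enrolment, and then the draw. "After the surgery, each patient will randomly take an unmarked, opaque, sealed envelope containing a piece of paper with a unique number", running from 1 to 38. "Then the numbers will be divided into two sets via computing software", and "All patients respectively entered the intervention group and the placebo group according to their own numbers". On treatment it says "Patients of the intervention group will receive ESWT at 6 months post-operatively", with sham given to the other group at the same time.

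Aim, design, and setting places allocation at the same stage: "The 1:1 allocation to either receive radial ESWT or sham-ESWT, after surgery is conducted using computer-generated random allocation sequences and sealed envelopes".

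Other sections that bear on the point:
- The abstract specifies an intention-to-treat comparison.
- Withdrawals lets patients leave at any time and lists tendon rupture and increasing regional pain among the reasons for discontinuation.
- Sample size allows a 20% loss of primary outcome data.
- Rehabilitation sets one programme for all patients.
- Statistical analysis puts the primary efficacy point at 6 months after surgery.
- Trial status says: "Recruitment began in October 2018 and the approximate date when recruitment will be completed in October 2021".

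**The concern.** Randomisation protects a comparison best when it takes place just before the treatments diverge. Here the operation and the rehabilitation are common to both arms, so for the first 6 months the trial is in effect a single cohort. Allocating at the start of that period brings no stated benefit and has two costs.

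First, events in the common period become post-randomisation events. Such a patient belongs to the intention-to-treat set without having reached the randomised treatment. With 38 patients there is little room for that.

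Second, the arm is fixed, and may be determinable, for months before it is needed. The primary outcome is a patient questionnaire, so early knowledge of the arm could affect retention or reporting before treatment starts.

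**Working it through.** **Inputs.** From Sample size: difference 6.5 points, SD 6.9, 15 per group, 20% loss, 38 in total. From Procedures: treatment at 6 months, last follow-up at 2 years. From Trial status: recruitment from October 2018 to about October 2021, or 36 months. The article gives no loss rate between surgery and the first session, so the rates below are assumptions.

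**The plan's own total.** 2 × 15 = 30, and 30 / (1 − 0.20) = 37.5, rounded up to 38. This reproduces. The article does not say how the 20% divides between the time before and after the first session.

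**Patients lost in the gap.**
- Loss even over 24 months: 20% × 6/24 = 5%, and 0.05 × 38 = 1.9, about 2 patients.
- Half of the loss in the first 6 months: 10%, and 0.10 × 38 = 3.8, about 4 patients.

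**What they do to the analysis.** Two cases must be kept apart.

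*Case A: never treated, outcomes still collected.* Assume that an ESWT-arm patient who never starts responds on average like a sham patient. The expected difference is then 6.5 × (1 − L), where L is the untreated fraction. The power is a two-sided 5% normal approximation with 15 per arm. The article does not state sidedness.

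| L | Expected difference | Power |
|---|---|---|
| 0% | 6.5 | 73% |
| 5% | 6.5 × 0.95 = 6.2 | 69% |
| 10% | 6.5 × 0.90 = 5.9 | 64% |

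The starting value of 73% reflects the two-sided test and is a separate matter. The relevant result here is the fall of about 4 to 9 percentage points.

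*Case B: never treated, no outcomes.* These patients do not dilute an observed mean difference; they reduce the number analysed.
- If the 20% already covers them, 38 × 0.80 = 30.4 patients remain and the planned 30 is still met.
- If they come on top of the 20%, the evaluable number per arm is 19 × (1 − L) × 0.80: 15.2, 14.4 and 13.7 for L = 0, 5 and 10%. Power on the same basis is 74%, 72% and 69%.

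**When the list must exist.** Read as one division of the numbers, the split cannot wait until all 38 have drawn, at about month 36 of recruitment, because the first patients are due for treatment about 6 months in. So it exists for about 36 − 6 = 30 of the 36 months (30/36 = 83%). With even recruitment (an assumption), about 0.83 × 38 ≈ 32 patients draw a number whose arm is already on a list, up to 6 months before their first session.

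**The case against.** The case against is substantial, and it limits what can be claimed.

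- **Timing.** A reader might infer that the draw happens immediately after the operation. The article says only that it follows surgery and gives no interval. An early draw is the natural reading, but no date is fixed.
- **Concealment at entry.** A reader might infer that allocation concealment fails. The documents do not support this. Consent, baseline assessment and surgery all come before the draw, and the envelopes are unmarked, opaque and picked at random. Entry cannot be selected by arm, and a number alone does not disclose one.
- **A contradiction.** A reader might see Aim, design, and setting as conflicting with Procedures. Both name computer generation and sealed envelopes, and the former does not say that the arm itself is in the envelope. The two accounts are compatible.
- **Early knowledge of the arm.** This needs one person to have both number and list. Who holds the list is a detail that an article may leave to the full protocol. The sham device, the exclusion of physiotherapists from assessment and the blinded collectors of outcome data all work against it.
- **Size.** The 20% margin may already cover losses in the gap, so no shortfall in the 38 is shown.
- **Late change.** The article appeared in November 2022 and still reports enrolment as open, although recruitment was due to end around October 2021. Few patients may remain to be allocated.

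All of these stand as limits. None supplies a reason to allocate before month 6 or removes the gap between allocation and treatment.

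**Conclusion.** The point holds as a modest, inexpensive design improvement. As written, allocation precedes the only difference between the arms by up to 6 months, and foreseeable losses in that time count as losses after randomisation.

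On the assumption of even loss, about 2 of 38 patients are affected; if half of the loss falls early, about 4. If they still give outcomes, an expected difference of 6.5 points becomes 6.2 or 5.9. If they do not, they use up loss margin, and whether the total then falls short cannot be told from the article.

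The number-to-arm list must exist during most of recruitment. That makes the arm determinable early, but nothing in the article shows that anyone treating or assessing patients has access to it.

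**What to change.** For patients not yet allocated:
1. Keep consent, baseline and surgery as they are. Open the allocation at the existing 6-month visit, after the 6-month assessments and immediately before the first session, in patients still in the trial.
2. State that the number-to-arm list is held by someone who neither treats nor assesses patients.
3. Reconcile Statistical analysis with this order. It sets the primary efficacy point at 6 months after surgery, but the 6-month VISA-A would then be the pre-treatment baseline.

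The present division of 1 to 38 can stay. An equal split already gives 19 per arm when all numbers are used, so permuted blocks are not needed.

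**Cost.** No visit is added. Patients lost before month 6 would not be randomised, so reaching 38 randomised would take 38 / 0.95 = 40 consents at a 5% early loss, or 38 / 0.90 = 42.2, rounded up to 43, at 10%. If the planned 20% already includes early losses, 38 consents still leave about 30 with outcomes.

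If some patients were already allocated after surgery, the trial will contain two allocation timings and hence two differently defined randomised sets. The report must say how many patients fall under each, and show losses before the first session by arm. If everyone has been allocated, what remains is that report of losses, a statement of when the list was made and who held it, and the reconciliation of the primary time point.

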### Percutaneous radiofrequency coblation

The symptomatic region will be identified and marked before the anesthesia. Then, the patient would accept a general anesthetic and be placed in a prone position. A grid with a 5-mm interval will be mapped out over the marked site [35]. A 1.5-mm Kirschner wire will be used to puncture the skin and make eyelet-sized holes. The radiofrequency probe (Topaz, ArthroCare, Sunnyvale, California) will be inserted and subsequently activated for 1 second with minimum power, hole by hole. If there exists another concomitant injury such as Haglund deformity, it will be recorded and addressed by endoscopic surgery at the same time. After completion of the procedure, a standard sterile dressing would be applied to minimize tension across the wounds.

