### Statistical analysis

All continuous data from primary and secondary outcome measurements will be summarized by descriptive statistics with the number of observations (*n*), mean, SD, minimum, median and maximum. Uncontinuous data such as co-morbidities concomitant injuries will be summarized by descriptive statistics with the number of observations, calculating the incidence separately and analyzing whether it is associated with prognosis. The primary point for analyses of efficacy will be 6 months after surgery, then 1 year and 2 years. A statistical software program (SPSS for Windows, version 23.0; SPSS Inc, Chicago, IL) will be used for statistical analysis in this study. Group comparison will be statistically analyzed by either Student’s *t* test or Mann-Whitney *U* test, depending on whether the data is normally distributed. The significance level will be set at a *p* value <0.05.

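### Concomitant endoscopic surgery is known before the draw and flagged as possibly prognostic, yet neither the allocation nor the group comparison uses it; the cost is precision and interpretability, not bias

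*Protocol article*

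**What the plan says.** - **Operation.** Under Percutaneous radiofrequency coblation, the protocol article states: "If there exists another concomitant injury such as Haglund deformity, it will be recorded and addressed by endoscopic surgery at the same time". The Exclusion criteria do not remove these patients, while the title and the stated aim describe the comparator as coblation alone.
- **Timing of the draw.** Under Procedures: "After the surgery, each patient will randomly take an unmarked, opaque, sealed envelope containing a piece of paper". Operation type is therefore fixed and recorded before allocation.
- **Allocation.** Also under Procedures: "Then the numbers will be divided into two sets via computing software". The numbers run from 1 to 38. The abstract has "patients allocated in a 1:1 ratio to one of two parallel groups". No stratification factor or minimisation is described.
- **Analysis.** Under Statistical analysis: "Group comparison will be statistically analyzed by either" a t test or a Mann-Whitney test, chosen by normality. Neither takes a covariate. For co-morbidities and concomitant injuries the same section plans "calculating the incidence separately and analyzing whether it is associated with prognosis", which is separate from the comparison of arms.

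**The concern.** The trial asks what ESWT adds to coblation, but the operation is not the same for everyone. The authors treat concomitant injuries as something that may affect outcome, and they hold the information before randomising. It nevertheless enters neither the allocation nor the treatment comparison.

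With 19 patients per arm, a visible difference in operation type between the arms is quite possible by chance. If the factor is prognostic, two things follow:

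- Variation that could be explained stays in the error term, which costs power.
- If the arms turn out unequal, readers will ask how much of the observed difference reflects the operation rather than ESWT. An adjustment chosen only after the imbalance has been seen is open to challenge.

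**Working it through.** **Inputs from the protocol article.** N = 38, split 1:1 (19 per arm). Under Sample size: "minimum clinically important difference (MCID) of 6.5 points for the VISA-A", SD 6.9, 5% significance, 80% power, 15 per group, 20% loss.

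**Assumptions, since the article gives neither figure.** K is the number of patients with added surgery, taken as 4 to 16 of 38 (11% to 42%), with 19 of 38 as a further check. g is the shift in VISA-A that goes with added surgery, taken as 3.25, 6.5 or 10 points.

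**1. The plan's own sample size.** With difference 6.5 and SD 6.9, a one-sided 5% t test at 80% power needs 14.66, so 15 per group, and 15/0.8 = 18.75, so 19 per group and 38 in total. This reproduces the stated figures. A two-sided 5% t test needs 18.70, so 19 per group before any loss. The power figures below are two-sided with all 38 patients analysed, where the unadjusted t test has power 0.81.

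**2. Chance of imbalance.** Under an unstratified 19:19 split, the number X with added surgery in one arm is hypergeometric (38, K, 19). The arms differ by |2X − K| patients.

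| K of 38 | Share | P(differ by 4 or more) |
|---|---|---|
| 4 | 11% | 0.105 |
| 6 | 16% | 0.180 |
| 8 | 21% | 0.232 |
| 10 | 26% | 0.269 |
| 12 | 32% | 0.295 |
| 16 | 42% | 0.325 |

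For odd K the difference can only be odd. With K = 15 or 19, a difference of 3 or more has probability 0.51 or 0.52, and one of 5 or more has probability 0.18 or 0.19. Over K = 4 to 19, the standard deviation of the difference in proportions is 10 to 16 percentage points.

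**3. Effect of a four-patient gap on the estimate.** Four of 19 is 21 percentage points. Shift = g × 4/19:

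- g = 3.25: 0.7 points
- g = 6.5: 1.4 points
- g = 10: 2.1 points

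For comparison, the MCID is 6.5 and the standard error of the difference at the planning SD is 6.9 × √(2/19) = 2.24.

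**4. Validity and power.** Trials of 38 patients were simulated, 6,000 runs per setting, with shares of 20%, 30% and 50%, total SD held at 6.9, an unstratified draw and a two-sided 5% level. With no ESWT effect, the unadjusted t test rejected in 0.047 to 0.053 of runs, which is the nominal level within simulation error. With a true difference of 6.5:

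| g | Unadjusted power | Adjusted for operation type |
|---|---|---|
| 3.25 | about 0.80 | 0.80–0.82 |
| 6.5 | about 0.80 | 0.85–0.88 |
| 10 | about 0.80 | 0.93–0.98 |

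These gains are for the operation-type term alone, before any overlap with the pre-ESWT score.

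**The case against.** The strongest reply is that nothing invalid is planned. Simple randomisation followed by an unadjusted test is sound, and operation type precedes a random draw, so any gap is chance that the standard error already covers. This stands. A reader might infer that the ESWT effect will be biased by, or confounded with, operation type. The documents do not support that: the shift in step 3 is one possible draw, equally likely in either direction, and even at g = 10 it is smaller than one standard error (2.1 against 2.24).

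A reader might also infer that added surgery moves VISA-A by more than the 6.5-point target. No section says so. The article only plans "analyzing whether it is associated with prognosis", without direction or size. Ten points is at the high end: g²p(1 − p)/6.9² shows that at K = 8, 12 or 16 it would account for 35%, 45% or 51% of the planning variance. At 3.25 points adjustment gains almost nothing.

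The factor is not ignored altogether, since it is recorded and examined separately. Part of its influence may also already show in the 6-month score, so the extra gain from a surgery term beside that score is smaller than step 4 shows and cannot be computed from the article.

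Finally, covariates are often left to a statistical analysis plan, and none is shown. That does not fully answer the point, because the article names the tests to be used, and those tests are unadjusted.

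**Conclusion.** The point holds as a matter of precision and interpretability. A factor that the authors regard as possibly prognostic, and know before allocation, is left out of both the draw and the comparison. The planned test is neither biased nor anti-conservative.

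The size depends on two figures the documents do not give. Over the assumed prevalence of 4 to 16 in 38, a gap of four or more patients arises in roughly one trial in ten to one in three. The resulting shift is 0.7 to 2.1 points, or about 11% to 32% of the MCID (0.68/6.5 to 2.11/6.5). The power gain from adjustment runs from negligible to substantial over the same assumed effects. The change is worth making because it is cheap and the data are already collected, not because a large distortion has been shown.

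**What to change.** 1. Replace the unadjusted primary test with a linear model (ANCOVA), specified before unblinding: VISA-A at a post-ESWT visit on treatment, with the 6-month pre-ESWT VISA-A and concomitant endoscopic surgery (yes/no) as covariates. State that the 6-month score is taken before the first ESWT or sham session, since the article places both at 6 months.
2. Report operation type by arm in the baseline table. Give the ESWT effect among coblation-only patients descriptively, since that is the comparison the title names.
3. Stratify only any allocations still to be made. Trial status gives recruitment from October 2018 with completion expected around October 2021, so there are probably few or none. The single list of 1 to 38 would also have to be reworked, so the covariate is the part to act on.

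Cost: about one degree of freedom per covariate, no new data, no change to N and no change to any procedure. If very few patients had added surgery, the surgery term will contribute little, but it should stay in as pre-specified.

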### Rehabilitation

Crutch will be recommended during the first 4 weeks after surgery. No immobilization is needed. In addition, all the patients will be encouraged to begin range of motion and isometric strength exercises immediately after surgery, and eccentric training will begin 6 weeks after surgery [36]. At the 4-week follow-up, the patients will be advised to wear regular shoe gear and continue the exercises. Patients shall be able to walk normally without any assistive device since the seventh week.

### Extracorporeal shockwave therapy

The patient will be lying on the stretcher in the prone position with barefoot, and the feet will be positioned towards the shock wave apparatus. The symptomatic area will be marked, then ultrasound gel will be applied on this region which the radial shock waves with a Dolorclast equipment (EMS Electro Medical Systems, Nyon, Switzerland), the intensity being 2000 pulses, 6–8 Hz of frequency, and 1.5–2.5 Bar of pressure per application. Compared with those of radial ESWT group, patients of the sham ESWT group will go through the same process with the same equipment, in which the apparatus’ therapeutic head will be installed a support. The support will block the propagation of shock waves without changing the equipment’s appearance, noise, and using process. Furthermore, the patients will feel the vibration of the machine, but the insertional region won’t be directly stimulated. Either the radial ESWT or sham ESWT will be administered 4 times at weekly intervals.

